### Study design

2.1

This will be a single-center, prospective, and parallel randomized controlled trial. Participants will be randomly assigned to a VIT or TIE group for corresponding interventions and follow-up. The study period will begin 1 week before discharge and include a 12-week follow-up after discharge. Outcomes will be measured at baseline (V0), after instruction (V1), before discharge (V2), and at week 12 after discharge (V3).

This trial is registered at ClinicalTrials.gov (registration number: ChiCRT2500097816) on 26/02/2025. The study protocol is reported according to the Standard Protocol Items: Recommendations for Intervention Trials 2013 (19) guidelines, and the intervention procedures are described according to the Consolidated Standards of Reporting Trials (CONSORT) 2025 Checklists. Figure 1 illustrates the CONSORT flow diagram for this study, and Table 1 summarizes the study schedule and assessments.

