### Study population and recruitment

2.2

All patients will undergo initial screening by physicians in the Department of Respiratory and Critical Care Medicine to confirm AECOPD diagnoses. Independent researchers will then conduct a secondary screening according to inclusion and exclusion criteria (Table 2) to ensure that only eligible patients are included. Patients or their legal guardians will be required to provide informed consent to participate.

**Table 2 T2:** Inclusion, exclusion, and withdrawal criteria.

**Inclusion criteria**	**Exclusion criteria**	**Withdrawal criteria**
(1) A previous pulmonary function test confirming a COPD diagnosis (postbronchodilator FEV1/FVC < 0.7) and currently hospitalization due to AECOPD	(1) Severe cognitive impairment; inability to understand assessments or instructions; and inability to comprehend the study's nature, scope, and potential consequences	(1) Hospitalization and receipt of treatment for non-AECOPD pulmonary diseases (e.g., lung volume reduction surgery, severe chest trauma) within 12 weeks after discharge
(2) Age = 40–85 years	(2) Bronchiectasis as the primary COPD manifestation	(2) Voluntary request to withdraw from the intervention or terminate follow-up observations
(3) Hospitalized patients with AECOPD who no longer meet GOLD 2025 criteria for respiratory failure or ventilatory failure.	(3) Complication due to malignancy	
(4) Continual, regular use of a fixed bronchodilator inhaler for >3 months after discharge	(4) A history of lung volume reduction surgery within 3 months before admission;	
(5) Use of an Ellipta, pMDI, or soft mist inhaler (SMI) as the inhalation device	(5) Severe diseases, such as heart, liver, kidney diseases, or hemodynamic instability	
(6) Provision of written informed consent	(6) Currently pregnant, breastfeeding, or planning to become pregnant during the study	

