### Randomization, allocation concealment, and blinding

2.3

All patients will be randomly allocated at a 1:1 ratio to either the VIT or TIE group by using a random number table generated by an independent statistical analyst with SPSS. In accordance with the 2025 WHO age classification, participants will be stratified into two age groups (40–65 years and 66–85 years) before randomization to ensure balanced distribution across intervention arms. The assignment details will then be sealed in opaque envelopes. After each participant provides written informed consent and completes their baseline assessments, the study coordinator will open the envelope to reveal the participant's group allocation.

Because of the nature of the intervention, neither the participants nor the instructors will be blinded; nevertheless, the outcome assessors and statistical analysts will remain blinded to group assignments.

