### Interventions

2.4

All patients will receive two inhaler usage instruction sessions during hospitalization and will be followed up weekly via telephone over 12 weeks after discharge. Researchers blinded to the group assignments will implement this measure. It will ensure regular use of inhalation medications in both groups during the study period and enable recording of any possible AE events and their severity.

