(7) Chronic activity-related dyspnea: This will be assessed using the modified Medical Research Council dyspnea scale.

(8) Inhaler medication adherence: The Chinese version of the Test of Adherence to Inhalers (TAI) will be used to assess treatment adherence. TAI scores, ranging from 10 to 50, are used to categorize adherence into three levels: low (≤45), moderate (46–49), and high (50). This scale has good reliability and validity (23).

(9) Health-related quality of life: This will be measured using the COPD Assessment Test.

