### Statistical analysis

2.7

Data analysis will follow the modified intention-to-treat principle to ensure complete randomization, minimize selection bias, and reflect real clinical practice. Missing data will be addressed using multiple imputation to reduce potential bias resulting from missing information, ensuring the robustness and accuracy of the analysis. All statistical tests will be performed according to a preestablished statistical analysis plan. SPSS (version 21.0) will be used for all data analyses, and two-tailed *p* < 0.05 will be considered to indicate statistical significance.

Continuous variables will be expressed as means ± standard deviations or median (Interquartile) where appropriate, and categorical variables as frequencies and percentages. Normality testing for continuous variables will be performed using the Shapiro–Wilk or Kolmogorov–Smirnov test, and homogeneity of variance will be assessed using the Levene test. For continuous variables that are normally distributed with equal variance, intergroup comparisons will be conducted using the independent-samples *t*-test. For continuous variables that do not meet the normality or homogeneity assumptions, the Mann–Whitney *U*-test will be employed. For discrete variables (such as the AE number and severity over 12 weeks), intergroup comparisons will be performed using the chi-square, Fisher exact, or Cochran–Mantel–Haensel χ^2^ test.

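### Inclusion criterion 4 asks for more than 3 months of inhaler use after discharge, which cannot be assessed at screening or confirmed at any scheduled visit

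*Protocol article*

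**What the plan says.** Protocol article, section 2.2 (Study population and recruitment), Table 2, inclusion criterion 4: "Continual, regular use of a fixed bronchodilator inhaler for >3 months after discharge". The same section says when the criteria are applied: "Independent researchers will then conduct a secondary screening according to inclusion and exclusion criteria (Table 2) to ensure that only eligible patients are included".

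Section 2.3 (Randomization, allocation concealment, and blinding) fixes the order of events: "After each participant provides written informed consent and completes their baseline assessments, the study coordinator will open the envelope to reveal the participant's group allocation". Table 1 places randomization at baseline (V0), and section 2.4 has both instruction sessions take place during the hospital stay, so allocation precedes discharge.

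Section 2.1 (Study design) sets the length of observation: "The study period will begin 1 week before discharge and include a 12-week follow-up after discharge". The last scheduled visit is V3, at week 12 after discharge.

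Inhaler use after discharge appears in two other places. Section 2.4 says of the weekly calls: "It will ensure regular use of inhalation medications in both groups during the study period". Section 2.5.2, item 8, makes adherence a secondary outcome: "The Chinese version of the Test of Adherence to Inhalers (TAI) will be used to assess treatment adherence". Table 1 schedules this test at V0 and V3.

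Section 2.7 (Statistical analysis) describes the analysis population: "Data analysis will follow the modified intention-to-treat principle to ensure complete randomization, minimize selection bias, and reflect real clinical practice".

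**The concern.** An inclusion criterion must be answerable yes or no when the patient is screened. This one concerns months that follow both screening and randomization, so a screener cannot truthfully record it as met.

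Two things are at stake. The first is who gets in. If criterion 4 means use before admission, it selects established inhaler users. If it means a planned prescription, a patient newly started on an inhaler also qualifies. Screeners could apply either reading, and a later reader could not tell which population was enrolled.

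The second is the randomized comparison. A criterion that can only be judged afterwards leaves room to declare a randomized patient ineligible in retrospect. The ground would be continued inhaler use, which comes after allocation. Participants are not blinded and both arms receive education, so continued use may differ by arm, and it may also be related to prognosis. Selecting on it would compare subgroups that randomization did not create.

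**Working it through.** The point rests on timing and on setting the protocol's statements side by side.

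**1. Order of events.**
- Screening against Table 2: during the index hospital stay (section 2.2).
- Consent and baseline assessments, then the envelope is opened: in hospital (section 2.3).
- Two instruction sessions: in hospital (section 2.4).
- Discharge, then 12 weeks of follow-up (section 2.1).
- The behaviour named in criterion 4: begins at discharge.

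Criterion 4 therefore lies wholly after screening and after allocation.

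**2. Can any visit confirm it?**
- Follow-up: 12 × 7 = 84 days.
- Three months: 365.25 / 4 = 91.3 days.
- Gap: 91.3 − 84 = 7.3 days.

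The criterion asks for more than 3 months, so even a patient who uses the inhaler without a break up to V3 has not yet met it. Table 1 has no later contact.

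**3. Does other text settle the meaning?** No sentence recasts the criterion as a prescription, an intention or prior use. Elsewhere Table 2 keeps the time frames apart: exclusion criterion 4 looks back 3 months from admission, and withdrawal criterion 1 looks forward 12 weeks from discharge. Exclusion criterion 6 shows how a forward-looking item can be made checkable, since it asks about a plan for pregnancy, which can be established at consent. Criterion 4 is not worded in that way.

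**4. What would literal enforcement do?** It could happen only after randomization, by removing patients who stopped or used the inhaler irregularly. The weekly calls would tend to bring such use to light, and the test of adherence at V3 measures it as an outcome. The analysis set would then be conditioned on a variable measured after allocation.

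**5. Does the sample size depend on it?** The inputs in section 2.8 are event rates of 48.9% and 15%, α = 0.05, 80% power and 20% dropout. With the unpooled two-proportion formula:

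n = (1.96 + 0.84)² × (0.489 × 0.511 + 0.15 × 0.85) / 0.339² = 7.84 × 0.3774 / 0.1149 = 25.7 per group

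25.7 / 0.8 = 32.2, which matches the stated minimum of 32, and 32 / 0.8 = 40 matches planned recruitment. No input refers to inhaler use after discharge, so rewording criterion 4 changes nothing here.

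The document does not say how many patients literal enforcement would remove. Taking a range as an assumption, power for 48.9% against 15% (two-sided, pooled variance under the null) is:

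| Analysed per group | Power |
|---|---|
| 40 | 91.7% |
| 36 | 88.6% |
| 32 | 84.6% |
| 28 | 79.3% |

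Lost power would be moderate. The larger problem is selection after randomization, which a bigger sample does not cure.

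**The case against.** The strongest reply is that criterion 4 is only loosely drafted. Table 2 is applied at screening, where the item can work only as planned or prescribed use. Much of the text fits that reading. The withdrawal criteria are two, hospitalization and treatment for a lung disease other than an exacerbation, and the patient's own request; stopping the inhaler is not among them. Irregular use is handled by telephone reminders. The adherence test at V3 has a low-adherence category, so poor adherers are expected to be still in the trial. Multiple imputation is planned, and the stated aims of the analysis include limiting selection bias. The 84-day follow-up also gives no occasion on which the rule could be enforced.

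Most of this stands, and it rules out three stronger inferences:
- A reader might infer that the trial will drop non-adherent patients. No sentence says so, and the points above suggest that they are kept.
- A reader might infer that the inclusion and withdrawal columns contradict each other. They do not: one governs entry and the other exit, and leaving non-use off the withdrawal list is consistent with retaining such patients.
- A reader might infer that the undefined modification of intention-to-treat is itself the fault. Its definition may sit in the separate analysis plan, which is not shown, so its absence here is not a finding.

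What the reply does not remove is the wording. A stated eligibility rule that cannot be applied when eligibility is decided is wrong as written. An analysis plan could protect the analysis set, but it could not make the criterion assessable at screening.

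**Conclusion.** The point holds as a defect in a stated eligibility rule. It is certain that criterion 4 cannot be assessed at screening and cannot be confirmed at V3, which falls about a week short of 3 months. Which of the plausible meanings was intended cannot be determined from the article.

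The threat to the randomized comparison is conditional: it arises only if the criterion is enforced literally after allocation. The document gives neither the number of patients who would be affected nor the relation between continued use and exacerbation risk, so no size of bias can be stated. Any figure would depend on assumed inputs.

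Severity: should-fix. The sample size is unaffected.

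**What to change.** Reword criterion 4 as a condition that can be verified at consent. One form is that a fixed inhaled bronchodilator is prescribed at screening with the intention to continue it through week 12. If prior use was meant, state use before admission and its duration. The investigators must say which meaning was intended.

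Add one sentence stating that later non-use or a change of device does not remove a randomized patient from the analysis, and leave adherence to the secondary outcome that already measures it.

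The cost is a one-line amendment to Table 2, the added sentence, and a re-check of the screening logs for any patients already enrolled, to see which reading was applied.

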## Abstract

**Background:**

Acute exacerbations (AEs) are key events in the progression of chronic obstructive pulmonary disease (COPD), accelerating the decline in lung function and increasing mortality considerably. Inhaler therapy is essential for COPD management; however, incorrect use of inhalation techniques can reduce drug efficacy and increase AE frequency. To optimize the effectiveness of inhaler use, we aim to conduct a randomized controlled trial, in which short-term visual instructions for inhalation use are provided to hospitalized patients with AE of COPD (AECOPD) to reduce AE frequency and severity within 12 weeks.

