### Sample size calculation

2.8

Our literature review indicated that the AE rate within 3 months after hospitalization for AECOPD is approximately 48.9% (5). Our preliminary data (unpublished) indicate that after VIT, the treatment failure rate at 90 days is approximately 15%. Therefore, the expected effect size between the two groups is about 33.9%. We set the significance level α = 0.05 and the statistical power at 80% (i.e., β = 0.20), with a dropout rate assumed to be 20%. The calculated values for *Z*_α_/2 and *Z*β are 1.96 and 0.84, respectively, with standard deviation σ = 0.614, effect size Δ = 0.339. Based on these parameters and sample size calculations, each group must include ≥32 patients. To ensure data accuracy and account for potential dropouts, we plan to recruit 40 patients per study group, totaling 80 participants.

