## Discussion

3

Inhaler technique is complex. Even after receiving appropriate education, many patients may use incorrect inhalation techniques due to a lack of detailed assessment of their equipment; this may reduce the efficacy of inhaled medications. Studies thus far have primarily observed the inspiratory flow rate in patients using DPIs to assess and guide optimization of inspiratory flow rate (18); however, research on the inspiratory flow rate in patients using pMDIs or SMIs is limited. We observed that when using a pMDI or SMI, most patients exhibited excessively high PIFrs (>80 L/min), increasing medication deposition in the oropharynx and thereby hindering effective drug delivery. Studies have reported that the error rate in inhalation techniques with pMDIs is as high as 86.7%, whereas that with SMIs is 58.9%. TIE primarily involves demonstration-based teaching: a physician first demonstrates the correct technique and key points to their patient; then, the patient mimics the technique under the physician's observation and guidance. However, with this technique, errors related to hand–mouth coordination and effective inhalation duration often remain undetected.

In this study, we will use sensors to monitor inhalation duration and hand–mouth coordination dynamically. With sensor feedback, physicians can provide targeted practice to address patient errors, overcoming the limitations of traditional education methods. To the best of our knowledge, this will be the first clinical study to objectively assess the entire inhalation process and offer targeted guidance for error correction. This will also be the first study to apply a visual method for inhalation technique instruction for patients with AECOPD. Visual feedback-based educational training methods have been widely applied in rehabilitation, with successful outcomes srehabilitation (24, 25), as well as in rehabilitation for pediatric cerebral palsy (26), orthopedic (27), and pain management (28).

Here, we primarily aim to observe and compare the impacts of our short-term VIT and the TIE on AECOPD frequency within 12 weeks after discharge. We anticipate that our results will provide evidence supporting the establishment of more effective inhaler technique education processes.

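### The AE comparison in section 2.7 uses no V0 technique score, although the scores are collected before allocation and the trial's premise links technique to exacerbations

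*Protocol article*

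**What the plan says.** Table 2 (section 2.2) sets entry by diagnosis, age, clinical status, regular inhaler use, device and consent. The device criterion is "Use of an Ellipta, pMDI, or soft mist inhaler (SMI) as the inhalation device". Nothing in the table refers to technique, PIFr or an error at V0.

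Table 1 schedules PIFr, EIT, EIV, IIFSs and the operation checklist at V0. Section 2.3 places allocation after V0: once the participant "completes their baseline assessments, the study coordinator will open the envelope". Randomisation is stratified by age only (40–65 and 66–85 years).

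The Abstract gives the mechanism: "incorrect use of inhalation techniques can reduce drug efficacy and increase AE frequency". The Discussion says how common errors are: "the error rate in inhalation techniques with pMDIs is as high as 86.7%, whereas that with SMIs is 58.9" per cent. No rate is given for Ellipta.

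Section 2.7 sets the comparison: "For discrete variables (such as the AE number and severity over 12 weeks"), the groups are compared by chi-square, Fisher exact or Cochran-Mantel-Haenszel (CMH) tests. It names no covariate and does not say what would define the CMH strata.

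**The concern.** VIT is meant to reduce AEs by improving technique. On the trial's own reasoning, a patient's technique at V0 should therefore predict AE risk, and may also predict how much that patient can gain from VIT. The score is measured before allocation in every randomised patient, so adjusting for it cannot introduce bias from post-randomisation events.

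Chi-square and Fisher exact tests cannot carry a covariate, and the CMH strata are left open. As written, the primary comparison loses whatever precision the score offers. With about 32 completers per arm, a chance imbalance in V0 technique would also go uncorrected.

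The second issue is interpretation. Patients with and without errors are pooled, and no estimate by V0 technique is planned. A null result would then give no indication whether VIT failed throughout or helped only those with errors. The trial aims to inform a pathway of assessment followed by education, so this split is of direct interest.

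**Working it through.** **1. The plan's own figure.** Inputs from section 2.8: control risk 0.489, VIT risk 0.15, difference 0.339, z-values 1.96 and 0.84, dropout 20%.

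- Variance term: 0.489 × 0.511 + 0.15 × 0.85 = 0.3774. Its square root is 0.614, the stated σ.
- n = (1.96 + 0.84)² × 0.3774 / 0.339² = 25.7 per arm.
- 25.7 / 0.8 = 32.2, which matches the stated 32. Then 32 / 0.8 = 40, the recruitment target. The dropout allowance appears to be applied twice, which leaves some margin.
- With 32 completers per arm at the planned risks, power is 0.85 (normal approximation, pooled variance under the null) or 0.79 (Fisher exact).

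**2. What adjustment could add.** In a linear approximation, a baseline covariate that explains a share R² of outcome variance multiplies the variance of the treatment effect by 1 − R². The document gives no R². For 32 completers to carry the information of 40, R² would need to be 1 − 32/40 = 0.20. Power at 40 per arm is 0.92, against 0.85 at 32. If R² is near 0, the gain is close to nil and the cost is one degree of freedom.

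**3. How many covariates the data can bear.** At the planned risks, patients with at least one AE number 32 × 0.489 + 32 × 0.15 = 15.6 + 4.8 = 20.4. Treatment, age stratum and one technique score are three terms, or about 6.8 such patients per term. That supports one technique covariate, not all five.

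**4. How small the error-free group would be.** Assume the Discussion's error rates apply here.

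- pMDI rate: 32 × (1 − 0.867) = 4.3 per arm.
- SMI rate: 32 × (1 − 0.589) = 13.2 per arm.

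Numbers of this size allow an estimate with a wide interval. They do not allow a useful interaction test.

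**5. Dilution, conditional only.** Assume that 33.9 points holds in patients with errors, that error-free patients gain nothing, and that the whole trial has one device's error rate.

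| Error-free share | Average difference | Power, 32 per arm | Fisher exact |
|---|---|---|---|
| 0 | 0.339 | 0.85 | 0.79 |
| 13.3% (pMDI) | 0.339 × 0.867 = 0.294 | 0.71 | 0.63 |
| 41.1% (SMI) | 0.339 × 0.589 = 0.200 | 0.37 | 0.30 |

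If the pilot behind the 15% was as unselected as the trial, 33.9 points is already an average over both kinds of patient, and the first row applies.

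**6. The ceiling in SMI users.** Let q be the AE risk of error-free patients under TIE, with overall risk 0.489. The largest possible difference, if VIT removed every AE in patients with errors, is 0.489 − 0.411q.

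- Equal risk, q = 0.489: 0.489 − 0.201 = 0.288, below 0.339.
- q = 0.30: 0.489 − 0.123 = 0.366, above 0.339.
- Break-even: q = 0.15 / 0.411 = 0.365.

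**The case against.** Three objections deserve weight.

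**The analysis plan may already cover this.** Section 2.7 refers to a pre-established statistical analysis plan, which is not shown, and covariates and subgroups are often left to such a plan. This limits the point: nothing in the article is wrong or contradictory. But the article does name the tests for AE number, and two of the three cannot use a baseline score. If the plan adjusts, the two texts need aligning.

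**Enrolling all users of the listed devices is legitimate.** Section 2.7 says the analysis is meant to reflect ordinary practice. Restricting entry to patients with a V0 error would change the population and slow recruitment. This objection stands, and no restriction is asked for.

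**Adjustment does not cure dilution.** This also stands. A covariate adds precision and corrects chance imbalance. It does not change who is averaged over.

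A reader might go further and infer that the trial is underpowered because error-free patients dilute the effect it is sized on, or that 33.9 points is unattainable in SMI users. The document supports neither:

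- Section 2.8 does not say whether the pilot patients had errors.
- The 28.8-point ceiling needs equal AE risk with and without errors, which sits badly with the premise that errors raise AE frequency. It no longer falls short of 33.9 points once error-free risk is about 36.5% or less.
- One minus the cited error rate is a doubtful measure of patients with nothing to correct. The Discussion also reports that most pMDI and SMI users inhaled too fast, which the visualised training addresses.
- TIE also trains to three correct attempts, so a V0 error does not by itself identify who gains from VIT over TIE.

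**Conclusion.** The point holds as an inexpensive improvement to the stated analysis, not as an error in the design. The primary AE comparison uses none of the V0 technique scores, although they are available before allocation and the trial's rationale makes technique prognostic. The gain depends on how strongly V0 technique predicts AEs. The document asserts that link but does not quantify it. The benefit runs from almost none up to the equivalent of 8 more completers per arm at R² = 0.20, and beyond that if the link is stronger.

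Because entry needs no technique error, the average effect may be smaller than the effect in patients with errors. Whether that weakens the sizing is unknown. Power of 0.37 to 0.71 applies only under the assumptions in step 5 and should not be read as the trial's power. Any estimate by V0 error status will rest on roughly 4 to 13 error-free patients per arm and can only be descriptive.

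**What to change.** In section 2.7:

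1. Make the primary AE comparison a regression model with three terms: treatment, age stratum (40–65, 66–85) and V0 IIFSs as a continuous covariate. Use a count model if the outcome is the number of AEs, or a binary model if it is any AE, and fix the choice in advance. The chi-square or Fisher test can stay as a supporting unadjusted result.
2. Report the VIT–TIE effect in patients with and without a V0 error, each with its confidence interval. Label this as descriptive, with no claim resting on an interaction test. Define V0 error in advance from the operation checklist and sensor feedback.

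In section 2.8, state whether the pilot patients behind the 15% had technique errors or were unselected, so that readers can judge whether 33.9 points is already an average.

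If the separate analysis plan already contains these items, bring section 2.7 into line with it.

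The cost is wording and one degree of freedom for the technique covariate. No visit, measurement or change of eligibility is needed.
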